### Study participants

#### Power and sample size

The primary outcome criterion of the study is to reduce mental stress of the women assessed by the brief symptom inventory (BSI-18). Former research reported healthy women to have a BSI-18 total score of 3–4 points, whereas mentally stressed women had 15–25 points [64]. After psychotherapy the BSI-18 total score was reduced by 10 points [65, 66]. Hence, assuming a medium effect size (Cohen’s d = 0.5 corresponding to a reduction by 7 points), a test-retest correlation of 0.5 between the baseline assessment and 26-week-follow-up, a significance level α = 0.05 and a power of β = 0.80, 27 women are required in each group. As telemedicine is an add-on focusing on stabilizing the effects of the psychotherapy, the second randomization into TIG and TCG is neglected in this calculation. However, envisaging 80 women for each group and assuming a drop-out-rate of 10%, 36 women are randomized to the TIG and TCG which is enough to analyze medium to large effects. Figure 1 shows the participant flow and the sample sizes of the different study groups.

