#### Subsequent allocation: telemedical intervention

After finishing the psychotherapy approximately 6 months after childbirth, women of the PIG are randomized either to the TIG or the TCG. Women of the TIG are regularly contacted by trained nurses via telephone call and additional short message to stabilize the effects of the psychotherapy and support the women in mastering daily life challenges [48, 59]. Whereas calls are made biweekly during the first 2 months and 4-weekly afterwards, short messages are sent weekly. The content of the telephone calls and short messages are leaned to the content of the psychotherapeutic intervention. The calls are semi-structured. During the first structured part, nurses assess the current mental health (BSI-18) as well as current positive and negative life events. In the second part, women have the possibility to discuss issues and projects in supportive dialogues.

The TCG is not receiving further interventions. The telemedical intervention lasts for 6 months and terminates the interventional part of the study.

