### Limitations and generalizability

Women of the control group are not treated within the study but are referred to professional assistance at the end of the study. Further, it is unknown yet how healthy women will react to childbirth and study procedures (regarding mental stress and endocrine changes). Hence, differences between groups might be diminished. All women are recruited in Western Pomerania, a more rural area of Germany with more socio-economic disadvantages and a higher prevalence of psychiatric and somatic diseases [62]. Thus, the study sample might be affected more significantly which would make the conclusions on mildly affected women more difficult.

In addition, the study sample is restricted in its representativeness by some of the exclusion criteria. Women with multiple pregnancies, major birth defects, alcohol or drug addiction, psychotic symptoms as well as suicidality are particularly in need of interventions, but excluded in this study. Further, teenage mothers are a special target group not considered in the present study. Due to the young age, teenage mothers often are overwhelmed by the new responsibilities and insufficiently progressed in their emotional and personality development [103].

Although the application of the psychotherapeutic intervention and study assessments is envisaged to take place in the study center at the University Medicine Greifswald, home visits will be offered. Not all women are recruited from urban regions and some might be unable to visit the study center due to socio-economic, medical or personal reasons [49, 52]. However, home visits are more time consuming and some of the study assessments (e.g., the immediate processing of blood sample to measure oxytocin levels) are not possible at home visits.

As the study is very comprehensive, the multiple assessments could elevate the maternal mental stress level which in turn can result in increased drop-out rates.

Although couple and family meetings are feasible during the individualized psychotherapy, the study interventions are focused on the mothers and not primary family based. Hence, the active role of the fathers might be understated. In addition, a recent study suggests that even maternal preconception mental health predicts infant outcomes [104]. Consequently, prevention and intervention programs might have to start earlier as in pregnancy, even in the preconception phase.

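### 36 women per telemedicine arm is called enough for medium effects, but at the plan's own medium effect (d = 0.5) power is below 80% on the figures it states: about 55% to 68% two-sided, 68% to 78% one-sided

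*Protocol article*

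**What the plan says.** All the planning figures stand in one paragraph of the protocol article, under Power and sample size.

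- Effect size: a medium effect is "Cohen’s d = 0.5 corresponding to a reduction by 7 points".
- Correlation: "a test-retest correlation of 0.5 between the baseline assessment and 26-week-follow-up".
- Error rates: "a significance level α = 0.05 and a power of β = 0.80", read here as power 0.80. Sidedness is not stated.
- Result for the main comparison: "27 women are required in each group".
- Second randomization: set aside in this calculation, because telemedicine is treated as an add-on.
- Planned numbers: "envisaging 80 women for each group and assuming a drop-out-rate of 10" per cent, followed by the statement that "36 women are randomized to the TIG and TCG which is enough to analyze medium to large effects".

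The Allocation section places the second randomization at six months postpartum, 1:1. On what follows, the section on the telemedical intervention says: "The telemedical intervention lasts for 6 months and terminates the interventional part of the study". The TIG versus TCG contrast at the end of telemedicine therefore falls at the 52-week visit. The limitations section adds that "the multiple assessments could elevate the maternal mental stress level which in turn can result in increased drop-out rates".

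**The concern.** The paragraph fixes what medium means and what power is wanted. It then declares 36 per arm sufficient from medium effects upwards, for a comparison it has just left out of the calculation. No power, test or effect size supports that declaration.

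Whether telemedicine stabilises the benefit of psychotherapy is a randomized question that the abstract puts forward. If the sample is described as sufficient for medium effects and the result is null, readers may conclude that telemedicine does not help, when a true d = 0.5 could easily have been missed.

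The timing adds to this. The number 36 is already net of the 10% loss, yet a further six months pass before the outcome is measured.

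**Working it through.** **1. Reproduce the plan's figure.** 80 × (1 − 0.10) = 72 women at the second randomization, and 72 / 2 = 36 per arm. This matches exactly, so the sentence is read as 36 in each arm.

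**2. Inputs.** n = 36 per arm, d = 0.5, alpha = 0.05 and target power 0.80 come from the sample size section. Two-sided testing is my assumption; one-sided is also shown. The correlation r = 0.5 is stated for baseline to 26 weeks only, and using it for 26 to 52 weeks is an assumption.

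**3. Method.** Two-sample noncentral t with 2n − 2 = 70 degrees of freedom. The noncentrality is d × √(n/2) unadjusted. For ANCOVA it is divided by √(1 − r²) = √0.75 = 0.866.

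- Unadjusted: 0.5 × √18 = 2.121
- ANCOVA: 2.121 / 0.866 = 2.449

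Normal check, two-sided: Φ(2.121 − 1.960) = 56.4% and Φ(2.449 − 1.960) = 68.8%. The exact values are slightly lower.

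**4. Power at d = 0.5**

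| Analysed per arm | Test | Unadjusted | ANCOVA, r = 0.5 |
|---|---|---|---|
| 36 | two-sided | 55.3% | 67.6% |
| 36 | one-sided | 67.6% | 78.3% |
| 32 (assumed further 10% loss: 36 × 0.9 = 32.4) | two-sided | 50.4% | 62.3% |
| 32 | one-sided | 63.1% | 73.9% |

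**5. Women per arm needed for 80% power at d = 0.5.** Two-sided: 64 unadjusted, 49 with ANCOVA at r = 0.5. One-sided: 51 and 38. All four exceed 36.

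**6. Effect detectable with 80% power, two-sided.** With 36 per arm: d = 0.670 unadjusted, and 0.670 × 0.866 = 0.580 with ANCOVA. With 32 per arm: 0.711 and 0.616.

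**7. Large effects.** At d = 0.8 with 36 per arm, two-sided power is 92% unadjusted and 97% with ANCOVA.

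**8. Correlation that would rescue d = 0.5.** Set the detectable effect equal to 0.5 with 36 per arm.

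- Two-sided: 0.670 × √(1 − r²) = 0.5, so √(1 − r²) = 0.747 and r ≈ 0.67. As a check, r = 0.7 gives 83%.
- One-sided: the unadjusted detectable effect is 0.592, so √(1 − r²) = 0.5 / 0.592 = 0.845 and r ≈ 0.54.

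**The case against.** **No power is claimed for this comparison.** The sentence speaks of medium to large effects and names no power. If it means effects lying between 0.5 and 0.8, the detectable d of 0.58 to 0.67 falls inside that span. This is the best defence, and it makes the fault one of wording rather than of calculation. But the usual reading includes the medium effect itself, and the same paragraph has just set that at 0.5 with a target power of 0.80.

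**The plan already says the second randomization is left out.** This stands. It means the sample size was never built on TIG versus TCG, and it limits the weight of the point. It does not support the statement that the number is nevertheless enough.

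**36 exceeds the 27 required.** The only match found for 27 is a one-sided paired test within one group (26.1, rounded up). The between-group variants in step 5 give 38 to 64. A paired test on 36 women does have 83% power two-sided, but it tests change within one arm, not the difference between arms.

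**Sidedness and the later correlation are not given.** This stands. One-sided testing with r = 0.5 falls short only slightly (78%), and r of about 0.54 would then reach 80%. Two-sided testing needs about 0.67. The BSI-18 is also taken at baseline and 8 weeks, and the statistical methods include repeated-measures and multilevel models, so using several earlier scores could raise precision. None of these conditions is stated, so 55% to 68% is a conditional range and not a fixed property of the trial.

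**Loss after 26 weeks.** A reader might infer that the trial ignores it. The documents do not allow that conclusion: Figure 1, which carries the group sizes, is not shown, and the limitations section recognises that drop-out may rise. What can be said is that the text spends the 10% before the second randomization and states no rate afterwards.

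**BSI-18 points.** It is tempting to translate the detectable effects into points using the implied SD of 7 / 0.5 = 14. That SD comes from the psychotherapy calculation, and nothing in the article shows that it applies to women who have completed therapy. The result is therefore left in units of d.

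**Conclusion.** The point holds as a correction to one sentence. On the figures the article states, 36 per arm does not give 80% power at d = 0.5, whether the test is one- or two-sided. Two-sided, a true medium effect would be missed in roughly one third to almost one half of repetitions (1 − 0.676 = 32% to 1 − 0.553 = 45%), before any loss after 26 weeks. The upper part of the claimed range is sound.

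The size depends on two-sided alpha, on r between 0 and 0.5 for 26 to 52 weeks, and on all 36 per arm being analysed. The 32-per-arm figures rest on an assumed further 10% loss.

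A reader might infer that the trial as a whole is underpowered. It is not shown to be: 80 × 0.9 = 72 per arm for PIG versus PCG exceeds the 64 needed at d = 0.5, unadjusted and two-sided. Nor does the defect require TIG versus TCG to be declared exploratory; that is a design decision for the trial team.

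**What to change.** Replace the statement that the number is enough for medium to large effects with the detectable effect and its assumptions, for example:

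> With 36 women analysed per arm, TIG versus TCG has 80% power for d of about 0.6 to 0.7 (two-sided alpha 0.05, correlation between 26 and 52 weeks of 0 to 0.5). Power for d = 0.5 is about 55% to 68%, and lower with loss after 26 weeks. The comparison will be reported as an estimate with a 95% confidence interval.

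If the team has a one-sided test or a higher 26-to-52-week correlation in mind, it should say so and recompute these figures. If it expects a particular loss after the second randomization, it should add the number expected to be analysed at 52 weeks.

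The cost is a change of wording. Sample size, allocation and interventions stay as they are. The stated property becomes less favourable, and a null telemedicine result is less likely to be read as proof of no effect.

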**Fig. 1 Fig1:**
[figure not shown]
Study procedure, assessments, interventions and flow diagram of the randomized controlled trial. Note: BL = Baseline (occurs at approximately 25–28 weeks gestation), DL = delivery, 8 W = 8-weeks-follow-up, 26 W = 26-weeks-follow-up, 52 W = 52-weeks-follow-up, n = number

#### Inclusions criteria

Pregnant women are included if they are between 17 and 45 years of age and at the end of the second trimester (25th to 29th week of pregnancy). For the psychotherapeutic intervention group (PIG) and the psychotherapeutic control group (PCG), mental stress is the primary inclusion criterion (BSI-18 total score ≥ 7 or BSI-18 sub scales ≥3 and/or psychiatric diagnosis according to the diagnostic interview (DSM-IV/ICD-10) [67]. In the control group of healthy women, women may not report elevated mental stress, neither in the screening questionnaire (BSI-18 total score < 7) nor in the clinical interview.

#### Exclusion criteria

Women with multiple pregnancies or foreseeable major birth defect of the fetus, as well as women experiencing symptoms of withdrawal, exhibiting low motivation for therapy, suffering alcohol or drug addiction, having severe psychosis or reporting suicidality will be excluded. In addition, women being submitted to a recent psychiatric or psychotherapeutic treatment (or another study including such treatments) have to be excluded in order to impede confounding of therapeutic effects. However, if women initiate psychotherapeutic treatment during the study, they will not be excluded from the study.

### Recruitment

According to the statistical office of the federal state of Mecklenburg-Western Pomerania, about 13,000 children are born in Mecklenburg-Western Pomerania per year thereof 25–30% in the study region Western Pomerania [62]. In Germany as a whole, the 12-month prevalence of psychiatric disorders was estimated at 30–35% including a 12-month prevalence of addictive disorders estimated at 5–10% [68]. Hence, we expect 20–30% of the pregnant women to have a mental illness, resulting in approximately 650 childbirths of mentally stressed women in Western Pomerania per year. It is aimed to screen 1600 pregnant women.

The screening procedure is staggered in two phases: i) Pregnant women at the beginning of their second trimester consulting gynecologists, obstetrics centers, hospitals and/or counseling centers receive information material and the primal screening questionnaire on site to assess the first set of in- and exclusion criteria (multiple pregnancies, age, pregnancy trimester, BSI-18 total score). This primal screening questionnaire is evaluated by the study staff. ii) Women who gave their written consent to be contacted and are eligible to the study are invited for a detailed assessment of the eligibility criteria at the end of their second trimester of pregnancy. Women meeting the inclusion criteria accomplish the baseline assessment afterwards. On this level, mentally stressed (BSI ≥ 7 and/or psychiatric diagnosis) and healthy pregnant women are recruited with a 2:1 ratio.

### Allocation

After the baseline assessment, mentally stressed women are randomly allocated to the psychotherapeutic intervention group (PIG) or the psychotherapeutic control group (PCG) with a 1:1 allocation ratio. Healthy pregnant women are assigned to the healthy control group (HCG).

Six months postpartum, women of the PIG are again randomized and receive either a subsequent telemedical intervention of 6 months duration (TIG) or not (TCG) with an allocation ratio of 1:1. An independent researcher who is not involved in the PriVileG-M trial prepares the allocation by the statistical software SAS Version 9.4 (TS Level 1 M3 Copyright© 2002–2012 by SAS Institute Inc., Cary, NC, USA) using a randomization list with simple random sampling.

### Blinding

Study information to participants includes information about the respective study arms and the randomized design. An independent researcher is responsible for the allocation by the SAS computer program. Participants, psychotherapists and telemedicine nurses are not blinded for the group allocation, but data collectors are not informed about group allocation.

### Interventions

#### Consultation

After study inclusion, all participants receive a semi-standardized consultation from a study psychologist. Medical and psychological information on pregnancy, childbirth, and puerperium are provided. The impact of one’s own health behavior on the (unborn) child is explained and discussed. Finally, the women receive advise about existing supply structures and assistance beyond the study (e.g. counseling centers, psychiatric out- and inpatient clinics, family assistance). Contact data of a consultant who can be contacted in crises situations are provided both verbally and in writing.

#### First level allocation: psychotherapeutic intervention

Women of the PIG are allocated to an individualized psychotherapeutic intervention based on the principles of cognitive-behavioral therapy (3–4 months prenatal) which lasts for up to 10 months (5–6 months postnatal). Utilization will be tracked to assess implementation adherence. Participants will receive up to 20 individual biweekly sessions of 50 min each. Although it is strived to implement most of the therapy meetings in the study center, home visits are possible if necessary due to the socio-economic or health conditions.

The aim of this psychotherapeutic intervention is to reduce mental stress and psychiatric symptoms and to enhance self-efficacy and self-confidence. The therapeutic intervention is based on behavioral and supportive elements, for instance, psychoeducation, social skills training, stress and emotion regulation. A high individualization of the therapy is planned to address the heterogeneity of psychiatric symptoms, socio-economic status and conflicts of the women. Similar to traditional psychotherapy, the content and process of the intervention are individually adjusted to the symptoms, needs, and progress of the women. Because the father of the child, the partner of the mother or other family members influence the well-being of the pregnant women, meetings with the couple or the family will be realized upon demand. In case of crises situations, the women have the opportunity to contact a clinical psychologist/psychotherapist and to demand a crisis meeting with their psychotherapist.

#### Subsequent allocation: telemedical intervention

After finishing the psychotherapy approximately 6 months after childbirth, women of the PIG are randomized either to the TIG or the TCG. Women of the TIG are regularly contacted by trained nurses via telephone call and additional short message to stabilize the effects of the psychotherapy and support the women in mastering daily life challenges [48, 59]. Whereas calls are made biweekly during the first 2 months and 4-weekly afterwards, short messages are sent weekly. The content of the telephone calls and short messages are leaned to the content of the psychotherapeutic intervention. The calls are semi-structured. During the first structured part, nurses assess the current mental health (BSI-18) as well as current positive and negative life events. In the second part, women have the possibility to discuss issues and projects in supportive dialogues.

The TCG is not receiving further interventions. The telemedical intervention lasts for 6 months and terminates the interventional part of the study.

### Assessments

All participants are investigated five times during the study from the end of the second pregnancy trimester (25th -29th week of pregnancy) until 1 year postpartum. The baseline assessment (BL) will take place between the 25th and the 29th week of pregnancy, the birth-follow-up at 24–72 h after delivery (0 W), the 8-week-follow-up at 8 weeks postpartum (8 W), the 26-weeks-follow up at 6 months postpartum (26 W) and the 52-weeks-follow-up 1 year postpartum (52 W). The baseline assessment, the 26-week- and 52- week-follow-up are followed each by an Ecological Momentary Assessment (EMA) lasting 10 days.

At the assessment points mental health, physical health and interaction of mother and infant are investigated using standardized interviews, questionnaires, video recordings and the extraction of biosamples. Additionally, process evaluation questionnaires and interviews are conducted. The development and health of the child is evaluated in a physical examination.

For an overview of the assessment time points and assessments made, see Fig. 1.

### Outcome measures

Table 1 shows the maternal and infant variables investigated at different time points during the study. They can be classified into medical, psychological, video, ecological momentary, laboratory and evaluation assessments as well as the documentation process of the treatments.

#### Medical assessments

Pregnancy complications, course of the delivery, and infant physical health are assessed using medical documentations of the mother (maternity records and the obstetric clinical records the so called “Mutterpass”) and the infant (child’s medical records, i.e. “U-Untersuchungsheft”). The „Mutterpass” is a medical record book for all German pregnant women that is completed by the gynecologist, the midwife, and the staff of the obstetric clinics [69]. The “U-Untersuchungsheft” includes information about the infant’s health and development that are assessed by the staff of the obstetric clinics and by pediatricians at routine pediatric examinations until the age of six [70].

Furthermore maternal health, infant health and feeding patterns are assessed through a structured maternal interview at each assessment point to obtain medical details. During an additional physical examination by a pediatrician at 8 W and 26 W neurological development, anthropometric measurement and physical examination focusing on skin, respiratory tract, abdomen and circulatory system will take place.

The children’s developmental levels, temperament and possible early regulatory problems are evaluated by a German Development Screening (NES) [71], a German questionnaire assessing problems of excessive crying along with sleeping and feeding difficulties (SFS) [72] and the German version of the Very Short Form of the Infant Behavior Questionnaire-Revised (IBQ-R) [73].

#### Psychological assessments

An overview of all psychological assessments is given in Table 1. Stress symptoms are assessed by different questionnaires: the BSI-18 [64, 74], a questionnaire about chronic stress (TICS) [75], a short questionnaire for recognition of stress-factors (KFB) [76] and the Coping Inventory for Stressful Situations (CISS) [77]. The RS-11 questionnaire is used to assess resilience as personality trait [78].

For the psychiatric diagnosis at the screening and baseline assessments, the Diagnostic Interview for Mental Disorders (DIPS) is used [67, 79]. The DIPS is a standardized interview assessing psychiatric disorders according to ICD-10 and DSM-V. In addition, symptoms of several mental disorders are assessed in detail: the Childhood Trauma Questionnaire (CTQ) is used to evaluate six early traumatic experiences and assesses individual’s understanding of their childhood trauma [80]. The Dissociative Experiences Scale-Taxon (DES-T) is applied for the assessment of pathological dissociative phenomena [81]. Depression symptoms are monitored by the Patient Health Questionnaire (PHQ-9) [82] and the Edinburgh Postnatal Depression Scale (EPDS) [83]. Worries are assessed with the ultra-brief version of the Penn State Worry Questionnaire (PSWQ) which evaluates pathological worries by 3 items [84]; and with the Cambridge Worry Scale (CWS) containing items about worries during pregnancy [85].

The NEO-FFI is a multidimensional personality inventory assessing individual differences in five dimensions, namely neuroticism, extraversion, conscientiousness, openness to experience and agreeableness [86]. Concerning social support and partnership status, a short partnership questionnaire (PFB-K) [87] and a brief form of the Perceived Social Support Questionnaire are used (F-SozU-6) [88].

There are two questionnaires assessing attachment in the adult women: the brief form of the Experiences in Close Relationships - Revised (ECR − RD 12) [89] and the Adult Attachment Scale in its revised version (AAS-R) [90, 91]. Mother-child bonding is assessed prenatal as well as postpartum. The Maternal Antenatal Attachment Scale (MAAS) evaluates the attachment of the mother with her unborn child [92]. The Postpartum Bonding Questionnaire (PBQ) is used to assess mother-infant bonding after childbirth [93].

Quality of life in general is monitored by the WHOQol-Bref [94]. The Mother-Generated Index (MGI) is used to assess qualitative as well as quantitative quality of life from pregnancy to the postpartum period [95]. The self-rated health status items examine the subjective perceived physical health of the women, in relation to the physical health of other pregnant women or young mothers [96]. Health Literacy is assessed by the HLS-EU-Q16 [97].

